## 10.2 Statistical Hypotheses

We hypothesize that differential dynamics in various fat depots: as SAT and VAT in response to two opposing dietary strategies mediate the beneficial metabolic effects during weight loss and regain phases.

## 10.3 Analysis Datasets

We will check the assumptions for all the statistical analyses to ensure that none were violated. We will perform intention-to-treat analyses, including all the participants, by imputing the missing observations for adipose tissues for the individuals with missing data at 18-months by the multiple imputation technique, with the following predictors: age, gender, baseline weight/ BMI and waist circumference at the end of the intervntion. For missing data of body weight, we will use the last observation carried forward.

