## 6.2 Study agent Accountability Procedures

# 7 STUDY PROCEDURES AND SCHEDULE

## 7.1 Study Procedures/Evaluations

### 7.1.1 Study specific procedures

**Magnetic Resonance Imaging (MRI)**

To assess body fat depots/deposits, we will perform a 45-minute 1.5-Tesla MRI (Ingenia 3.0 T, Philips Healthcare, Best, the Netherlands) scans at baseline and after 18 months. In a sub-set of, randomly selected, 50% of the participants, we will perform MRI measurement after 6 months of intervention. The scanner utilize a 3D modified DIXON (mDIXON) imaging technique without gaps (2mm thickness and 2mm of spacing), fast-low-angle shot (FLASH) sequence with a multi-echo two-excitation pulse sequence for phase-sensitive encoding of fat and water signals (TR,3.6ms; TE1,1.19ms; TE2,2.3ms; FOV 520×440×80mm; 2×1.4×1mm voxel size). Four images of the phantoms will be generated, including in-phase, out-phase, fat and water phase. A breath-hold technique will be used to avoid motion artifacts when the chest and abdomen will be scanned. In all simultaneous fat depots quantifications and comparisons, observers will be blinded to time point and group treatment. All fat depots will be assessed by one or two raters. To validate our mDIXON quantification of fat ratio, we will test five tubes filled with 0%, 25%, 50%, 75% and 100% of oil to observe a linear relation.

***Abdominal fat depots:*** We will quantify abdominal fat using the MATLAB-based semi-automatic software. We will calculate mean VAT and SAT from three axial slices: L5-S1, L4-L5 and L2-L3. Quantification of the fat mass regions will include the area of each fat type and its proportion (percentage) of the total area of all fat types.

***Hepatic fat content:*** We will quantify the percentage of hepatic fat using PRIDE software from Philips Medical Systems. We will calculate mean percentage from four 2D slices (3cm intervals divided into quarters) by utilizing the region of interest (ROI) approach, which is based on measurements of tissue densities (fat/fat+water) using the Fat Ratio Calculation.

***Resting metabolic Rate (RMR)*** We will mesure RMR by indirect calorimetry (QUARK REE by COSMED, Rome, Italy) in which the quantity of oxygen consumed and carbon dioxide produced are measured and converted into kcal using the Weir equation.

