**Clinical measurements**

Height will be measured at baseline, to the nearest millimeter by using a standard wall-mounted stadiometer. WC will be measured at baseline, after 6 months (prior to the second randomization), and at 18 months, to the nearest millimeter with an anthropometric measuring tape; the measurement will be made half-way between the last rib and the iliac crest. Body weight will be measured monthly without shoes to the nearest 0.1kg. Fasting blood samples will be taken at baseline and at 18 months, at 8:00am, and will be stored at ‑80°C. Fasting plasma glucose (FPG) will be measured by Roche GLUC 3 (hexokinase method). Plasma insulin will be measured with an enzyme immunometric assay [Immulite automated analyzer, Diagnostic Products, coefficient of variation (CV)=2.5%]. Serum total cholesterol (CV=1.3%), high-density-lipoprotein cholesterol (HDL-c), low-density-lipoprotein (LDL) cholesterol, and triglycerides (CV=2.1%) will be determined enzymatically with a Cobas 6000 automatic analyzer (Roche). Plasma leptin levels will be assessed by ELISA (Mediagnost, CV=2.4%). All biochemical analyses will be performed at the laboratories of the University of Leipzig, Germany.

Changes in resting metabolic rate (RMR) will be performed, using a handheld indirect calorimeter^52^.

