## 10.4 Description of Statistical Methods

### 10.4.1 General Approach

Results will be presented as means ± SD unless otherwise stated. Analysis of variance with a covariance (ANCOVA) test will be used in order to assess adherence to the interventions (attendance of the group sessions) and differences in changes nutrient intakes between the diet strategies. General linear models will be used to compare the trajectories of body weight and WC across the four intervention groups. We will use multivariate two-way ANCOVA and compare type of diet and physical activity as fixed factors (2*2 factorial design) to test changes in specific fat depots, using mean of differences and 95% CIs for each intervention group over time. Optional interactions between diet and exercise will be assessed by the ANCOVA models. To assess the effect of the combination of diet and PA, general linear models will be used with LFPA– as the reference. All models will be adjusted for age, sex, baseline abdominal obesity and 18-month weight change. Changes in the various fat depots and deposits will be evaluated both as absolute and relative changes. The association between changes in abdominal fat and intra-hepatic fat, and changes in levels of blood biomarkers will be tested using multivariate linear regression models, adjusted for age, sex, weight change, intervention group and baseline abdominal fat status (for the abdominal fat models) or baseline intra-hepatic fat (for the hepatic model). Homeostasis-model-assessment-of insulin-resistance (HOMA-IR) will be calculated according to the following equation: insulin (U/ml)×fasting glucose(mmol/liter) ÷22.5. Statistical analysis will be performed with IBM SPSS (version 23). All *P*-values will be two-sided, and *P*<0.05 will be considered statistically significant.

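### The imputation model for missing 18-month fat depots omits diet and physical activity (PA), so the intention-to-treat effects shrink toward zero by up to roughly the missing fraction

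*Protocol*

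**What the plan says.** Protocol Section 10.3 promises an intention-to-treat analysis that keeps every participant by filling in absent 18-month fat-depot values through multiple imputation. The model for this is specified "with the following predictors: age, gender, baseline weight/ BMI and waist circumference at the end of the intervntion". The section gives no rule for a missing waist; last observation carried forward is stated for body weight only.

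Section 10.4.1 sets the analysis model. It will "compare type of diet and physical activity as fixed factors (2*2 factorial design) to test changes in specific fat depots", with possible diet-by-exercise interactions, and "All models will be adjusted for age, sex, baseline abdominal obesity and 18-month weight change".

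On timing, Section 7.1.1 gives MRI "scans at baseline and after 18 months" for everyone, with a month-6 scan in a random half. For waist it says "WC will be measured at baseline, after 6 months (prior to the second randomization), and at 18 months". Section 7.3.5 marks the early termination visit as not applicable, and Section 5.4.2 says that withdrawals are not replaced.

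**The concern.** An imputation model should contain every term that the analysis model estimates. Here the two randomised factors are missing from it. The missing values of both diet arms, and of both PA groups, are then drawn from one common distribution given the listed predictors. Age, sex and baseline weight or BMI are fixed before randomisation and cannot carry a treatment effect. The only listed variable that can is the end-of-intervention waist.

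At stake is the primary visceral fat (VAT) comparison. The imputed part of the sample dilutes the estimated diet and PA effects, in the analysis meant to be the most faithful to randomisation. The list also leaves out 18-month weight change, which is a covariate in every model, and covers baseline abdominal obesity only indirectly through baseline weight or BMI.

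**Working it through.** **Inputs from the protocol.** Target difference 3.57 cm², two-sided alpha 5%, power 80%, total 250 (Sections 10.4.1 and 10.5); 125 per diet (Section 10.6.1).

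**Inputs assumed.** The fraction *f* missing at 18 months is not stated. The nearest figures are the adherence rates in the investigators' earlier trial (Section 2.1): 95% at 1 year and 85% at 2 years. Linear interpolation to 18 months gives (95 + 85)/2 = 90%. Adherence there is not MRI completeness here, so I show 5%, 10% and 15%. Missingness is taken as unrelated to the outcome given the predictors, and equal across arms.

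**The plan's own figure.** No SD is stated, so 250 cannot be reproduced independently. Solving backwards for 125 per arm: SD = 3.57 / [(1.96 + 0.84) × √(2/125)] ≈ 10.07 cm². Read as about 62 per cell, the same sum gives about 7.1 cm². The proportional shrinkage below does not depend on either value; the power figures do.

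**Algebra.** Let δ be the true effect and *s* the share of it that the imputation model transmits through waist.

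Expected estimate = (1 − *f*)δ + *f*·*s*·δ = δ[1 − *f*(1 − *s*)]

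If waist is missing, or is itself imputed from the other listed variables, *s* = 0 and the estimate is δ(1 − *f*):

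| *f* | Expected effect (cm²) | Ratio |
|---|---|---|
| 5% | 3.57 × 0.95 = 3.39 | 0.95 |
| 10% | 3.57 × 0.90 = 3.21 | 0.90 |
| 15% | 3.57 × 0.85 = 3.03 | 0.85 |

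If waist is observed and transmits half the effect (*s* = 0.5), the ratio at 15% is 1 − 0.15 × 0.5 = 0.925. The same algebra applies to PA.

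**Simulation of the diet effect.** Three simulations agree.
- First, 125 per arm, no arm and no waist in the imputation: ratios 0.89 at 10% and 0.86 at 15% missing. With waist known and carrying half the effect: 0.94 at both. With arm included: 1.02 and 1.00.
- Second, 2×2 design with waist also missing: ratios 0.94–0.98 at 5% and 0.84–0.89 at 15%. Adding diet, PA, baseline VAT and baseline waist gave 0.96–1.03. Monte Carlo error on these ratios is about 0.02 to 0.03. With waist observed and half the effect assigned to it, the listed model gave 0.84–0.87 at 15%. Its benefit therefore depends on how waist is modelled, which the protocol does not inform.
- Third, with and without adjustment for weight change: 0.94–0.96, 0.90–0.92 and 0.83–0.86 at 5%, 10% and 15%, and about 1.0 once arm is included.

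**Power, on the back-solved SD.** At 15% missing, the first simulation gave 62% with the listed predictors (waist unavailable) and 72% with arm included. The second, imputing the change, gave 59–65% and 69–74%. For comparison, a complete-case analysis has 106.25 per arm: SE = 10.07 × √(2/106.25) = 1.38, 3.57/1.38 − 1.96 = 0.62, power about 73%. At these assumptions the planned imputation does worse than no imputation.

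**Baseline VAT.** In the second simulation, imputing 18-month VAT and then deriving the change, with an assumed baseline SD of about 40 cm², raised the pooled SE at 15% missing from about 1.4 to about 3.1 cm². The ratio stayed at 0.84–0.89, so this omission costs precision and does not cause the shrinkage.

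**The case against.** **The waist may often be available.** A reader might infer that nobody with a missing scan will have an 18-month waist. The documents do not support that. Participants are employees, most measurements are done at the workplace (Sections 4.1 and 5.3), and waist needs only a tape, whereas the MRI is a 45-minute scan. Someone who attends month 18 and misses only the scan can have a waist value, and it recovers part of the effect. The protocol does not say how missing scans divide between full dropout and scan-only loss. The point stands for true dropouts. If waist is strictly a predictor, they cannot be imputed at all and the promise to include everyone fails. If waist is imputed from the other listed variables, it carries no arm information.

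**Omitted baseline VAT as a cause of the bias.** It is tempting to blame it as well. The calculation shows otherwise: the shrinkage comes from leaving out diet and PA.

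**The size is not fixed by the protocol.** This is correct. Quoting 15% missing, or any single power loss, as the trial's expected result would go beyond the text. The simulated ratios are for diet; shrinkage of the PA effect rests on the algebra.

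**The direction is conservative, and an analysis plan may add detail.** Shrinkage toward zero does not create false positives in the main comparisons. But the protocol does not leave the predictors open: it states a list, and the list omits the tested factors.

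**Imputing with arm has its own assumption.** It takes dropouts to keep their arm's effect, which may be too favourable if they abandon the diet or the gym. This stands, and the fix must address it.

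**Conclusion.** The stated imputation rule is wrong as written. It omits the randomised factors that the primary model tests, so the estimated diet and PA effects are pulled toward zero. Where the 18-month waist is unavailable, the shrinkage is about the missing fraction: 3.57 cm² becomes about 3.39, 3.21 or 3.03 at 5%, 10% or 15% missing. Where waist is observed it is smaller, by an amount the protocol gives no basis to fix. This rests on data missing at random, equal missingness across arms and an assumed missing fraction. The power figures rest further on an SD that the protocol does not give and should be read as illustration. The loss of precision from omitting baseline VAT is real but separate.

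**What to change.** Replace the predictor list in Section 10.3 so that 18-month depots are imputed with:
- diet arm, PA arm and their interaction, or separately within randomised group;
- the baseline value of the same depot;
- all analysis-model covariates, including weight change;
- interim data already collected: month-6 waist, month-6 MRI where scanned, and monthly weights.

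Impute the 18-month waist jointly with the depots instead of treating it as a complete predictor. State how participants who leave before the month-6 PA randomisation enter the imputation and the 2×2 analysis, since they have no PA assignment. Add a sensitivity analysis for data missing not at random, in which dropouts do not keep their arm's effect.

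The cost is a wording change and a somewhat larger imputation model. No new data collection is needed.

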*There are several comparable dietary strategies to induce weight loss, but their effect on specific abdominal fat depots is unclear*. The effectiveness for weight loss^18-20^, and superiority for cardiovascular benefits^21^ of low-fat diets components is debated. Recently we completed a 2-years intensive workplace-based Dietary Intervention Randomized Controlled Trial (DIRECT)^22^ among 322 participants, who were assigned to three intervention arms - Low-fat diet, Mediterranean diet (MED), and low-carbohydrate (low-carb) diet. Adherence was 95% at 1 year and 85% at 2 years. The results [see details in the preliminary (c.3.) and figures sections] suggest that whereas the low-carb diet was superior in improving lipid profile and weight loss, the Med diet (high in mono-unsaturated fat-MUFA) provided the largest decrease in circulating insulin and glucose levels. All three arms induced similar dynamics in weight, revealing a weight-loss phase (0-6 months) and a subsequent regain-plateau (6-24 months) phase (N Engl J Med 2008). Specific loss of VAT mass has mostly been shown in response to exercise training^23^. Gene expression of adiponectin in VAT and SAT is modified by physical training^24^. However, dietary strategy to preferentially promote loss of VAT is unknown. Several lines of evidence suggest differential roles of macronutrients in the *accumulation* of intra-abdominal (visceral) adipose tissue. VAT cells have a two-fold higher glucose uptake rate and de-novo lipogenesis capacity compared with SAT cells^25^. Glucose-stimulated insulin secretion may also have preferential effects on VAT, as insulin-stimulated glucose uptake and lipogenesis, and the stimulation of the expression of 11-β-HSD1 with resulting increase in active cortisol, are more evident in VAT, enhancing VAT accumulation^26^. Feeding rats with a high sucrose diet increase not only muscle insulin resistance, but also VAT mass^27^, at least partly by promoting cell hypertrophy^28,29^. In a 4-week intervention study among 22 human obese subjects, a larger decrease in VAT measured by computed tomography was observed in the low-carbohydrate diet group compared to the high-carbohydrate diet group^30^. *It is therefore possible that reducing carbohydrate load may preferentially decrease VAT accumulation*. In contrast, dietary fat explained only two percent of the variance in general adiposity, and was unrelated to VAT mass when measured in cross-sectional studies^31^. A recent study on 42 monkeys compared diets containing either monounsaturated fatty acids or an equivalent diet containing trans-fats for 6 years^32^. It was shown that trans-fat-fed monkeys gained significantly more weight, associated with increased intra-abdominal fat deposition and insulin resistance, compared to monkeys fed diet rich in monounsaturated fatty acids. In humans, in a cross-sectional study among 334 female twins there was no relationship between total dietary fat composition and adiposity^33^. However, in women at low genetic risk of abdominal obesity, subjects with higher polyunsaturated fat intakes had about 50% less central abdominal fat than subjects with lowest intake. Thus, a suggested preventive strategy for VAT accumulation may include limiting dietary carbohydrates and apparently, increasing monounsaturated fats^34^. Therefore, some evidence suggests that VAT accumulation may be linked to carbohydrate load in the diet, whereas the fat load (accept for trans-fatty acids) plays a minor, or even protective role (in the case of monounsaturated fat). *However, large-scale intervention trials assessing whether limiting carbohydrates and increasing monounsaturated fat can assist in inducing VAT loss beyond the weight loss induced by conventional hypocaloric diet are required to establish the relationship between dietary macronutrients composition, intraabdominal adiposity and insulin resistance.*

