# 3 OBJECTIVES AND PURPOSE

***Objective 1:***  To assess the effect of Low-carb/MED and Low- fat diets with or without PA on the dynamics of body fat compesition (mainly VAT) during weight loss and regain-plateau phases by 1.5-Tesla MRI.

***Objective 2:***  To assess the effect of Low-carb/MED and Low- fat diets with or without PA on the dynamics of abdominal suncotenius intra-hepatic fat among participants with abdominal obesity or dyslipidemia.

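### Carrying the last body weight forward conflicts with the loss-then-regain-plateau course the protocol expects, and the filled values enter every model through 18-month weight change

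*Protocol*

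**What the plan says.** Section 10.3 gives two rules. Fat-depot values are filled for people "with missing data at 18-months by the multiple imputation technique", using age, sex, baseline weight or BMI, and waist circumference at the end of the intervention as predictors. For weight the rule is different: "For missing data of body weight, we will use the last observation carried forward".

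The expected course of weight appears in three places. Section 2.1 reports that the arms of the team's previous workplace diet trial behaved alike, "revealing a weight-loss phase (0-6 months) and a subsequent regain-plateau (6-24 months) phase". Objective 1 in section 3 studies fat "during weight loss and regain-plateau phases by 1.5-Tesla MRI". The hypothesis in section 10.2 is that fat-depot dynamics "mediate the beneficial metabolic effects during weight loss and regain phases".

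Weight is collected often. Section 7.1.1 says "Body weight will be measured monthly without shoes to the nearest 0.1kg", and the schedule in section 7.3.7 shows a weight at every month from 0 to 18.

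Section 10.4.1 uses weight twice: its trajectory is compared across the four groups, and "All models will be adjusted for age, sex, baseline abdominal obesity and 18-month weight change". Under section 10.1 the main endpoint is VAT, and the secondary outcomes are abdominal subcutaneous and hepatic fat. Sections 4.1 and 10.6.1 place the randomisation to added physical activity (PA) after six months of diet.

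**The concern.** Carrying a value forward is reasonable only if weight would not have changed after the last visit. The protocol says that it will change, and it sets out to study that change. Three things follow.

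- Someone lost near month 6 is given an 18-month weight close to the lowest point, so the later regain is removed from that person's record.
- Someone lost soon after the second randomisation carries a weight taken before PA began or barely into it. Whatever PA would have done to that person's weight is set to zero in the PA comparison.
- The filled weight becomes the 18-month weight-change covariate. In the VAT models a multiply imputed outcome then sits beside a covariate filled once and treated as known.

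At stake are the estimated 18-month weight loss, the description of the regain phase, the four-group weight comparison and, less directly, the adjusted VAT comparisons.

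**Working it through.** The protocol states no figure for the effect of this rule, so there is none to reproduce. The check asks in which direction the rule errs, and how far.

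**Inputs from the protocol.** Loss to month 6, then regain-plateau (2.1, 3, 10.2). Weights monthly to month 18 (7.1.1, 7.3.7). No dropout rate is given for this trial. The nearest proxy is the previous trial: "Adherence was 95% at 1 year and 85% at 2 years". Straight-line interpolation gives 95 - (95 - 85) x 6/12 = 90% at 18 months, or about 10% lost. Treating adherence as retention is itself an assumption.

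**Assumptions.** Mean weight falls in a straight line to a peak loss L at month 6, and a fraction r of L is regained in a straight line by month 18. People who leave would have followed this mean course. I take r = 0.2 to 0.5, L = 4 to 8 kg and dropout d = 10 to 30%.

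**Formulas.** Change from baseline at month t:
- t up to 6: w(t) = -L x t/6
- t from 6 to 18: w(t) = -L + r x L x (t - 6)/12
- at month 18: w(18) = -L x (1 - r)

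Error for one person lost at month t = w(t) - w(18). A negative value means that loss is overstated.

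**Where the sign changes.** Setting -L x t/6 = -L x (1 - r) gives t = 6 x (1 - r), which is month 4.8, 4.2 or 3.0 for r = 0.2, 0.3 or 0.5. Before that month loss is understated. After it, loss is overstated.

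**Mean error per person lost, as a share of L:**

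| Months of dropout | r = 0.2 | r = 0.3 | r = 0.5 |
| --- | --- | --- | --- |
| 1 to 3 | +0.47 | +0.37 | +0.17 |
| 5 to 8 | -0.15 | -0.24 | -0.43 |
| 6 only | -0.20 | -0.30 | -0.50 |
| 6 to 17 | -0.11 | -0.16 | -0.27 |
| 12 to 17 | -0.06 | -0.09 | -0.15 |
| 1 to 17, evenly | +0.01 | -0.06 | -0.19 |

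If regain is complete by month 12 and weight is flat after that, the 12-to-17 row becomes zero.

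**Error in an arm mean** = d x (error per person as a share of L) x L. With d = 0.10 and L = 6 kg:
- all lost at month 6: 0.10 x 0.20 x 6 = 0.12 kg to 0.10 x 0.50 x 6 = 0.30 kg, loss overstated (true loss 4.8 to 3.0 kg);
- all lost in months 1 to 3: 0.10 x 0.167 x 6 = 0.10 kg to 0.10 x 0.467 x 6 = 0.28 kg, loss understated;
- evenly over months 1 to 17: from 0.01 kg understated to 0.11 kg overstated.

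Over the whole assumed range (d = 10 to 30%, L = 4 to 8 kg), dropout all at month 6 overstates loss by 0.08 to 1.20 kg, and dropout all in months 1 to 3 understates it by 0.07 to 1.12 kg.

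**The PA comparison.** For people lost at month 6 the carried value contains no effect of PA. If 10% of each PA group leaves then, and they would have shown the same later PA difference as the others, the estimated difference is 0.9 of the full one. This does not require dropout to differ between groups.

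**The case against.** A reader might infer that all dropouts are frozen near their lowest weight, so that loss is overstated overall. The protocol does not support this. Only people who leave near month 6 are frozen near the lowest point. Those on the plateau are little affected, and the protocol speaks of a regain-plateau, not of a continuing rise. Those lost in the first months may have their loss understated.

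Two considerations make overstatement more likely, without settling it. People who leave before month 6 may never receive a PA assignment, so dropout within the four-group comparison may fall mostly at or after month 6; the protocol does not say how earlier leavers are handled. In the previous trial the fall in adherence was also larger in the second year. Early leavers might, moreover, return to baseline, in which case the rule overstates their loss too. The documents do not say which applies.

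A reader might also infer a definite bias between arms from unequal dropout. Nothing in the protocol indicates that dropout will differ by arm, so any such figure would be assumed.

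The other objections stand in part. Weight is neither the primary nor a named secondary endpoint. The VAT imputation uses baseline weight or BMI, not 18-month weight, so imputed VAT does not itself inherit carried-forward weights; the only route is the covariate. Using different methods for weight and fat is not an error in itself, since the scans follow a sparser schedule than the monthly weights. None of this defends the no-change assumption.

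**Conclusion.** The point holds in a limited form. The protocol fixes a rule whose assumption contradicts its own expected course of weight. The rule tends to overstate 18-month loss for people lost from about month 6 until the plateau, and may understate it for people lost in the first months. The net sign and size are unknown. About 0.1 to 0.3 kg per arm in either direction is an illustration that rests on 10% dropout, a 6 kg peak loss, 20-50% regain and dropouts following the mean course. None of these is given for this trial.

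The effect on the VAT models has a clear route, the weight-change covariate, but no derivable size or direction. Treating a filled value as observed also ignores its uncertainty; how much that matters is not quantified here. The change is worth making before analysis, but it does not by itself put the primary endpoint in doubt.

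**What to change.** In section 10.3, replace carrying forward as the main method for weight:

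- **Weight as an outcome.** Use a likelihood-based mixed model on all monthly weights, with baseline weight as covariate and diet by month throughout. PA and diet-by-PA terms enter only after month 6, because the PA groups do not exist before then.
- **Weight as a covariate.** Where 18-month weight change is used and month-18 weight is missing, fill it by multiple imputation from all earlier monthly weights and the assigned group, jointly with the fat-depot imputation. For anyone lost before the second randomisation, only the diet assignment can be used.
- **Carrying forward.** Keep it at most as a sensitivity analysis.

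No new data are needed, since weight is already measured monthly. The cost is a change of wording, a little more analysis work and possibly slightly wider intervals. The remedy does not depend on which way dropout timing would push the error.
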